## Methods and design

### Study population

#### Patients

Eligible candidates are end-stage renal patients who have been referred to the pre-transplant clinic and are currently listed on the wait list for a DDKT and who do not have a potential living donor yet. This includes patients (>18 yrs) newly referred for transplant preparation as well as patients who are already listed. Patients who are mentally incapable (e.g. mental deterioration, schizophrenic) or those with a compromised medical condition who are unable to withstand the intervention will not be included.

#### Invitees

Individuals in the social network of the patients are also invited to take part in this study. This practice is in line with the multisystemic approach of MST. For the invitees there are no limits set to ethnicity or the relationship with the patient. The number (≥1) of invitees (>18 yrs) participating will depend on the number that responds to the invitation of the patient.

### Design & procedure

In this prospective RCT all patients will be invited to participate by the educators after the consultation with the transplant nephrologists. During the face-to-face informational consultation the patient will receive written and verbal information on the aims and procedures of the study. Spouses, relatives or friends accompanying the patient to the hospital may be present during this consultation. Our target is to include 80 patients of Dutch origin and 80 patients of non-Dutch origin in the study over a period of two years in order to compare effectiveness of the intervention among these two groups. With respect to the inequality in LDKT, patients of non-Dutch origin will inherently be overrepresented in the study. After informed consent is obtained, patients will be randomized to either the control or the experimental group. The control group will receive standard care. The experimental group will receive standard care plus a home-based educational intervention. In the face of the equity principle, we will provide all the study materials (e.g. brochures, questionnaires) in the six most common foreign languages in the Rotterdam municipality namely, English, Arabic, Turkish, Papiamento, Portuguese and Modern Hindi [29].

#### Control condition

Patients assigned to the control group will receive standard care only. In the standard care all patients visiting our pre-transplantation outpatient clinic receive a consultation with a transplant nephrologist, a transplant coordinator, and a social worker. Additional to this verbal information, the patients receive a variety of written educational material and a DVD regarding various living donation and transplantation programs. All materials are translated in the six afore mentioned foreign languages. They can study this material in the coming four weeks before their second visit to the outpatient clinic during which they have the opportunity to ask additional questions. Additionally, our patients are invited to attend 4–6 times a year informational meetings held in the various regional hospitals. The baseline and post-measurements will be either handed out by the educators during the hospital visit or sent via mail. If necessary the educators may help in completing the questionnaire. The questionnaires are also available in six languages.

#### Experimental condition

The intervention consists of two sessions at the patient’s home. Session One: Firstly, at the beginning of the session the patient completes the baseline measurement. Secondly, the family network of the patients will be depicted on a genogram the educator in order to get familiar with the family structure and to recognize the values of that social system. The observation of the educators during the sessions represents an important source of information about how the present individuals relate to each other. In fact, the educators never rely solely on the individual’s verbal self-description to investigate social relations. Only by observing how the individuals behave with each other can the educators support or reject hypotheses based on self-reports. During this first session the educators watch for non-verbal clues that confirm or contradict what the social system is telling them. As the educators form tentative hypotheses about psychosocial hurdles, they do not offer advice or share their observations to avoid defensiveness. They rather focus on engagement by showing helpful interest while listening to the needs of the individuals and reinforcing the strengths of the respective social system. At the end of the first session the educators will make an inventory of individuals that the patient will invite for the second session. The educators may help in inviting identified individuals. The invitation will be conducted verbally accompanied by a brochure containing the 1) study purpose, 2) education content, and 3) contact information of the educators.

Session Two: The educators organize this session in such a way that they will do ‘what ever it takes’, in line with one of the basic principles of MST, to make this event as patient-tailored as possible. This means that the intervention will usually take place in the evenings and weekends since most friends and family members are working during office hours. The primary goal of this intervention is educational, therefore, it is not necessary that all the invitees are potential donors. The baseline-outcome measurement for the invitees will take place at the start of the second session. In exceptional cases multiple sessions are required in order to reach the goals set for those sessions. Table
1 shows the topics that will be discussed during the second session.

**Table 1 T1:** The educational topics discussed in the second session

		
	1 Introduction	The purpose of the Kidney Team At Home-study
	2 Kidney disease	An introduction to kidneys and kidney diseases
	3 Dialysis	The various forms of dialysis
	4	Morbidity and mortality associated with dialysis
	5	The psychosocial consequences of a kidney disease and dialysis
	6	The advantages and disadvantages of dialysis compared to kidney transplantation
	7 Transplantation	The medical evaluation in preparation for donor nephrectomy and kidney transplantation
	8	The various programs of donation and transplantation (DDKT and LDKT)
	9	The number of DDKT and LDKT performed nationally and locally
	10	The differences in ethnicity regarding access to LDKT
	11	The differences in graft survival between DDKT and LDKT
	12 LDKT	Additional advantages and disadvantages of LDKT
	13	The risks and psychosocial aspects associated with donor nephrectomy
	14	The personal, emotional and financial aspects of LDKT for the recipient
	15 Discussions	Whether present individuals have considered donation of their kidney

During both sessions at the patients’ home we will use the therapeutic framework of MST in order to stimulate open communication between the patient and the family members and to use and profit of the strengths and possibilities of the natural network of the patient. The objective of MST is to achieve a lasting consensus on the patient’s goals and how these goals can be reached with engagement and/or support of his/her social ecology. Such long-term consensus can not be achieved if the interpersonal relations, personal autonomy and feelings of those involved are not sufficiently considered. Therefore, creating a ‘safe’ environment during the intervention is regarded as an important aspect of a successfully implemented intervention. The licensed psychologist who will be implementing this protocol is certified in practical systemic therapy. Both the psychologist and the transplant coordinator (educators) will be supervised by an official MST supervisor throughout the study period.

In order to minimize hurdles for participation interpreters are used when Dutch is not the primary language of those present. The interpreter will also help patients and invitees with questionnaires or understanding the informed consent if that may ease the transfer of information. At the end of the second session the patient and the invitees will receive the post-measurement. This questionnaire can be completed immediately or returned via the mail within a week. In Figure
1 one can find the graphical depiction of the RCT.

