**Methods and design:**

All patients (>18 yrs) that are referred to the pre-transplantation outpatient clinic are eligible to participate in the study. Patients will be randomly assigned to either an experimental or a control group. The control group will continue to receive standard care. The experimental group will receive standard care plus a home-based educational intervention. The intervention consists of two sessions at the patient’s home, an initial session with the patient and a second session for which individuals from their social network are invited to take part. Based on the literature and behavioural change theories we hypothesize that reducing hurdles in knowledge, risk perception, subjective norm, self-efficacy, and communication contribute to well-informed decision making and reducing inequality in accessing LDKT programs. A change in these factors is consequently our primary outcome-measure. Based on power calculations, we aim to include 160 patients over a period of two years.

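### The patient baseline for the primary outcome is taken after randomisation, with the arm known, and by a different route in each arm

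*Protocol article*

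**What the plan says.** The order of events is given in *Design & procedure*: "After informed consent is obtained, patients will be randomized to either the control or the experimental group". No measurement is placed between the two steps.

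The patient baseline is then described separately for each arm.

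- *Experimental condition*: "The intervention consists of two sessions at the patient"'s home, and in the first of them "at the beginning of the session the patient completes the baseline measurement". The genogram and the rest of the session come afterwards. On language help: "The interpreter will also help patients and invitees with questionnaires or understanding the informed consent if that may ease the transfer of information".
- *Control condition*, in a paragraph about patients already assigned to control: "The baseline and post-measurements will be either handed out by the educators during the hospital visit or sent via mail". On help: "If necessary the educators may help in completing the questionnaire".

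The post-measurement in the experimental arm is given at the end of session two: "This questionnaire can be completed immediately or returned via the mail within a week".

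The abstract (*Methods and design*) says of the psychosocial factors: "A change in these factors is consequently our primary outcome-measure". The *Knowledge* section defines a clinically significant change as 8 points from baseline together with passing a cut-off of 17. *Statistical analysis* plans a mixed model for repeated measures.

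**The concern.** A baseline protects a randomised comparison only if allocation cannot have influenced it. Here it can, by several routes:

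- **Knowledge of the arm.** Most primary measures are self-reports: attitude, self-efficacy, subjective norm, risk perception, intention and communication. The example communication item asks about recent conversations. A patient who expects a family session at home may already be talking more.
- **Setting, mode and help.** One arm answers at home at the start of an educators' visit. The other answers at the hospital or by post. Help from interpreters is described for the home sessions, and help from educators for controls.
- **Standard education already read.** Newly referred patients receive written material and a DVD to study over four weeks. Their knowledge score at baseline depends on when in that period the form is completed, and nothing ties that moment to the same point in both arms.

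If any of these shifts the baseline in one arm, the shift enters the estimated effect on the primary outcome. The planned baseline comparisons between arms could not tell it from chance imbalance.

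**Working it through.** **Step 1. Order of events, experimental arm.** Consent, then randomisation (*Design & procedure*), then home session one, then baseline as its first step (*Experimental condition*). Session one exists only for allocated patients. The baseline therefore follows allocation and the patient knows the arm. This is explicit in the text.

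**Step 2. Order of events, control arm.** The hospital-or-post route is given for assigned controls only, and experimental patients follow another route. Since the route depends on the arm, allocation must come first. This is an inference, but a firm one. The date of the control baseline is not stated, so no time gap between arms can be calculated.

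**Step 3. How a baseline shift enters the effect.** The plan has no figure of its own on this point. Its 78 per group comes from transplant proportions that the article does not give, so it cannot be recomputed, and the point does not depend on it.

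Let the baseline in one arm be shifted upward by *b* SD, with no true effect, equal SDs and baseline-to-post correlation ρ. In SD units, the contrast of that arm against the other has:

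- Change from baseline: bias = −*b*; standard error = √(2(1−ρ)) × √(2/n)
- Baseline-adjusted: bias = −ρ*b*; standard error = √(1−ρ²) × √(2/n)

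**Step 4. Illustration.** From the documents: a total of 160 and two-sided α of 0.05. Assumed: equal arms (160/2 = 80), *b* and ρ. With *b* = 0.2 and ρ = 0.5, √(2/80) = 0.158.

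- Change: standard error = 1.000 × 0.158 = 0.158; 0.2/0.158 = 1.26; rejection probability 0.244.
- Baseline-adjusted: bias 0.5 × 0.2 = 0.10; standard error = 0.866 × 0.158 = 0.137; 0.10/0.137 = 0.73; rejection probability 0.113.

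False-positive rate (nominal 0.05), change / baseline-adjusted, 80 per arm:

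| Shift *b* | ρ = 0.3 | ρ = 0.5 | ρ = 0.7 |
|---|---|---|---|
| 0.1 SD | 0.083 / 0.055 | 0.097 / 0.065 | 0.129 / 0.095 |
| 0.2 SD | 0.188 / 0.068 | 0.244 / 0.113 | 0.372 / 0.236 |
| 0.3 SD | 0.361 / 0.092 | 0.475 / 0.195 | 0.688 / 0.460 |

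With 78 per arm, the central case gives 0.239 and 0.111. If the baseline were taken before allocation and in the same way for everyone, the expected *b* would be 0 and the rate would return to 0.05.

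**The case against.** The best defence is that the baseline is the first step of session one, before the genogram and before any teaching. That stands: the intervention itself does not contaminate it. It is also fair that questionnaires are translated for both arms, that some help exists in both, and that neither a post-measurement comparison without baseline nor the transplant outcomes depend on this baseline. Finally, the shift in the working is assumed. Calculating how often an assumed bias reaches significance does not show that the bias exists.

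A reader might infer more than the text supports:

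- *That patients never visited cannot enter the primary model because they have no baseline.* A repeated-measures mixed model can use a record with only a post-measurement, and the educators will ask drop-outs for one. What excludes unvisited patients is the modified intention-to-treat definition in *Statistical analysis*, which is a separate matter.
- *That posted control baselines, filled in beside the brochures, create an apparent benefit.* Controls may receive both measurements by post, so such inflation could occur twice and partly cancel in the change. Experimental patients may also post their second questionnaire.
- *That the arms always sit at different points in standard education.* Patients already on the wait list are eligible too, and the four-week reading period need not be running for them.

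Figure 1, which depicts the design, is not available here. If it shows another order, it contradicts *Experimental condition* and the two must be reconciled.

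**Conclusion.** The point holds for the patient baseline. In the experimental arm it is explicitly collected after allocation with the arm known. In the control arm it is collected by another route with no shared time point, and there the timing after allocation is inferred. Because the primary outcome is change from this baseline, any arm difference caused by allocation passes into the effect: in full for a change contrast, and by about ρ if baseline is adjusted for. Which of the two applies depends on how the mixed model treats baseline.

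The size and the sign of any bias are unknown. The figures of 24% and 11% rest on an assumed 0.2 SD shift, correlation 0.5, equal arms of 80 and no true effect. They show sensitivity and do not estimate what happened. The documents do not show that the trial is biased in a particular direction. They show a route to bias that no later analysis plan can close, because it lies in when and how the data are collected.

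**What to change.** Have every patient complete the same translated questionnaire at the consent contact, after consent and before the allocation is drawn, with the same help available to all. In *Experimental condition*, delete the baseline step from session one. In *Control condition*, remove the baseline from the sentence on hospital or postal delivery, leaving the post-measurement there.

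Where a patient cannot complete the form at the contact, let it be returned before allocation and record the mode of completion. Unsupervised completion then remains possible, but it cannot depend on the arm.

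The cost is a longer consent contact, language help at that contact (which the article describes for the home sessions), and the loss of a few patients who never return the form and so are not randomised. That loss deserves watching among patients with a language barrier, whom this trial particularly wants to reach. The questionnaires and translations already exist.

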##### Communication

Patients and invitees are asked if and how often they talk about kidney diseases and RRT with their family and friends. The development and selection of these questions was based on the validated ‘Family Functioning Questionnaire’ [36]. This questionnaire is designed to pinpoint the way families communicate and make choices regarding psycho-educational interventions. For example, ‘*How often have you recently talked with the people close to you about kidney transplantation from a living donor’ (1 = never - 5 = very often).*

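### Setting and timing anchor of the primary questionnaires differ by arm, so the primary comparison can mix the intervention effect with how and when it is measured

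*Protocol article*

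**What the plan says.** Design & procedure puts allocation directly after consent: "After informed consent is obtained, patients will be randomized to either the control or the experimental group".

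For the experimental arm, the Experimental condition section places the sessions at home: "The intervention consists of two sessions at the patient’s home". At session one, "at the beginning of the session the patient completes the baseline measurement". The second questionnaire follows the teaching: "At the end of the second session the patient and the invitees will receive the post-measurement", and "This questionnaire can be completed immediately or returned via the mail within a week".

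For the control arm, the Control condition section says: "The baseline and post-measurements will be either handed out by the educators during the hospital visit or sent via mail". It gives no interval or window. A second clinic visit about four weeks on is mentioned, but neither questionnaire is linked to it.

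The Objectives section names knowledge and communication as the primary research question. The example item under Communication reads: "How often have you recently talked with the people close to you about kidney transplantation from a living donor", scored 1 to 5.

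**The concern.** A randomised comparison of questionnaire scores is interpretable when both arms are measured in the same way at comparable times. Here the experimental arm is measured when a home session starts and when one ends. The control arm is measured around a clinic visit or by post. An arm difference can therefore reflect the place of completion, how recent the teaching was, or the fact that a group conversation has just been held, as well as any effect of the intervention.

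Communication is the most exposed outcome. Session two gathers people from the patient's network to talk about transplantation, and it closes with whether those present have thought about donating. A question about recent talk with people close to the patient, answered as that session ends, can count the session. Knowledge is exposed in a different way, because the test follows teaching on the same subjects by at most a week. These are the two outcomes in the primary research question.

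**Working it through.** The plan gives no figure on this point. Its only sample-size figure, 78 per group, rests on LDKT proportions from an earlier study that the article does not report. Pairs as different as 0.10 vs 0.29 and 0.50 vs 0.73 both give 78 (two-sided 0.05, 80% power, continuity correction). The figure can be neither confirmed nor refuted, and nothing below depends on it.

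**Step 1. The two schedules side by side**

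| | Experimental | Control |
|---|---|---|
| Baseline, when | after randomisation, start of session one | not stated; may also follow randomisation |
| Baseline, where | home | hospital visit or mail |
| Post-measurement, when | 0 to 7 days after session two | not stated |
| Post-measurement, where | home, or returned by mail | hospital visit or mail |
| Help described | interpreter | educators, if needed |

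The anchors differ: home sessions in one arm, clinic visit or post in the other. Mail and help with completion appear in both.

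**Step 2. What the contrast estimates.** Let b be the part of a mean score due to measurement conditions. The difference between arms in mean change is

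true effect + (b at post − b at baseline, experimental) − (b at post − b at baseline, control).

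An additive effect of setting that stays constant within an arm cancels. What does not cancel is anything that changes between baseline and post in one arm only. Having just left session two is such a change. The mixed model in the Statistical analysis section cannot separate it from the intervention effect, because it is tied to arm.

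**Step 3. Scale of the consequence, on assumed shifts.** The inputs are 160 patients split equally, 160/2 = 80 per arm (1:1 assumed), two-sided alpha 0.05, and no true effect. For a net shift of b SD,

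rejection probability = Φ(b/√(2/n) − 1.96) + Φ(−b/√(2/n) − 1.96), with √(2/80) = 0.158.

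| Assumed shift (SD) | 80 per arm | 40 per arm (one origin group, 80/2) |
|---|---|---|
| 0 | 5% | 5% |
| 0.1 | 9.7% | 7.3% |
| 0.2 | 24.4% | 14.5% |
| 0.3 | 47.5% | 26.9% |
| 0.5 | 88.5% | 60.9% |

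Worked line for 0.2 SD and n = 80: 0.2/0.158 = 1.265; Φ(−0.695) + Φ(−3.225) = 0.244.

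For comparison, the difference detectable with 80% power at 80 per arm is (1.960 + 0.842) × 0.158 = 0.44 SD. On the 1 to 5 communication item, half a category with an assumed SD of 1.2 is 0.5/1.2 = 0.42 SD. The communication outcome has several questions, so a shift on one of them would be diluted. None of these shifts comes from the article.

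**The case against.** A fair defence has several parts.

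- **Timing.** A reader might infer that the arms are shown to be measured at different times. The documents do not support that. The control interval is unstated, Figure 1 is not shown, and the article condenses a fuller protocol. What is shown is that the anchors are unmatched in the visible text.
- **Baseline.** A reader might take the post-randomisation baseline as an arm difference. It is not shown to be one, since control baselines are described for patients already assigned. It remains a weakness, because patients may know their allocation when they answer.
- **Mode and help.** The modes overlap, because mail is possible in both arms. Educators may help controls, and the questionnaires exist in six foreign languages. Interpreter help is described under the experimental condition, but it also covers consent, which precedes allocation. It does not follow that measurement is worst for non-Dutch patients.
- **Estimand.** Prompting family talk is the aim of the sessions, and patients invite people between sessions one and two. Some early change in communication is therefore real, and treating all of it as artefact would be wrong. Measuring at the end of an educational programme is also a recognised short-term choice.
- **Direction.** A reader might infer bias in favour of the intervention. A control questionnaire completed near a consultation or with educator help could also score higher, so the direction cannot be proved.

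These points limit the claim. They do not remove the session-end measurement, which the article states outright, or the lack of a common anchor in the text.

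**Conclusion.** The point holds in limited form. As written, setting and timing anchor of the primary questionnaires are tied to arm, and the item on recent talk can partly register session two. The size of any bias cannot be derived. An upward shift in the experimental arm is plausible for communication and for recall of freshly taught facts, but it is not demonstrated.

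The illustration shows only that modest shifts would matter: 0.2 to 0.3 SD gives about 24% to 48% false positives, assuming 80 per arm, 1:1 allocation, no true effect and a shift that does not cancel. If Figure 1 or the full protocol gives matched intervals, the timing concern shrinks to the recency of session two. This is an inexpensive improvement to the primary comparison, and it is not evidence that the trial's result would be wrong.

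**What to change.** - **Baseline.** Have all patients complete it at the consent consultation, before randomisation, and adjust each primary outcome for its own baseline value.
- **Post-measurement.** Give it in both arms at the same interval counted from randomisation, set so that session two is normally complete. The article offers no basis for a particular length, so the sponsor should choose and state it.
- **Mode and help.** Allow the same completion options, and the same translation, interpreter or educator help, in both arms.
- **Session-end form.** Keep it, if wanted, only as an experimental-arm process measure.

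The questionnaires, translations and mailing already exist, so the change is mainly to protocol wording and the assessment calendar. The price is some added non-response to the post-measurement and slightly more logistics at the consent visit. The non-response needs attention because the analysis population in the Statistical analysis section requires at least one post-baseline measurement. Knowledge gains may also look smaller than they would at session end.

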##### Intention

This factor measures the extent to which patients and invitees plan to / are willing to discuss RRT’s or if they would give or accept a kidney [25,26]. For example: *‘How much do you want to donate a kidney to the patient’ (1 = not at all - 5 = very much).*

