### Ethical considerations

The Medical Ethical Committee of Erasmus Medical Center, Rotterdam, The Netherlands, has approved this study, registered under MEC-2011-004 / NL34535.078.10. Firstly, the ethical feasibility of an intervention as we propose in this protocol had been evaluated. In that research it had been argued that an active intervention in peoples’ live is justified [46]. The proposed education and therapeutic counseling in this protocol needs to be relative to the social context and the personal condition of the subsequent patients in order to ensure ethical justification. Secondly, in our center we have recently published an article on the ethical considerations of such a home-based educational intervention for kidney patients and their social network [47]. The authors concluded that a home-based approach is ethically justified when certain essential conditions had been satisfied. We consider the following as the most important: 1) participation must be completely voluntary at any point during the intervention, 2) the intervention must not be persuasive (i.e. advocating for a certain treatment option), and 3) the goal and the procedure of the intervention must be clear to all participants.

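### Only the experimental arm may complete the post-questionnaire at the group session, so patients' attitude, self-efficacy, subjective norm and intention scores may carry a network-presence effect

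*Protocol article*

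**What the plan says.** **Experimental arm** (Experimental condition). "At the end of the second session the patient and the invitees will receive the post-measurement". The next sentence gives two routes: "This questionnaire can be completed immediately or returned via the mail within a week". The second session is the one to which the patient's social network is invited. The last entry in its topic table is "Whether present individuals have considered donation of their kidney". On language support, "The interpreter will also help patients and invitees with questionnaires". The patient's own baseline is taken at the start of session one. The invitees' baseline is taken at the start of session two.

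**Control arm** (Control condition). "The baseline and post-measurements will be either handed out by the educators during the hospital visit or sent via mail". It continues: "If necessary the educators may help in completing the questionnaire".

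**Outcomes** (Primary outcome measures). Attitude, self-efficacy, subjective norm and intention are all listed as primary and are all rating scales. Patients rate, among other things, accepting a living donor's kidney and discussing treatment with family and friends. The example intention item, for invitees, is "How much do you want to donate a kidney to the patient".

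**Ethics** (Ethical considerations). One condition is that "participation must be completely voluntary at any point during the intervention".

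**The concern.** The four outcomes ask what a person would say to, accept from or feel able to discuss with people close to them. An experimental patient may answer at the end of an evening when those people have gathered and donation has just been raised. A control patient answers at a clinic visit or at home, without such a gathering. If the setting moves the answers, the movement enters the between-arm difference and is read as an effect of the education. Randomisation does not protect against this, because the difference arises after allocation through the collection rule itself.

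Invitees raise a separate question: whether someone asked how much they want to donate can answer candidly, and feel free to do so, with the patient close by.

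**Working it through.** **Step 1: compare the collection rules.**

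| | Experimental patients | Control patients | Invitees |
|---|---|---|---|
| Baseline | Start of session one | Hospital visit or mail | Start of session two |
| Post-measurement | End of session two on the spot, or mail within a week | Hospital visit or mail | End of session two on the spot, or mail within a week |
| Invited network gathered at post-measurement | Yes, if completed on the spot | No | Yes, if completed on the spot |
| Contact with educators | Yes | Yes: they may hand out the form and help | Yes |
| Counterpart in the other arm | Controls | Experimental patients | None described |

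The row that separates the arms is the gathered network. Educator contact occurs in both. The abstract describes session one as being with the patient, so an experimental patient's baseline and post-measurement may also differ in setting. Controls have the same routes at both times. The text on session one does speak of individuals present, so some company at baseline cannot be excluded.

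**Step 2: which outcomes are exposed.** Attitude, self-efficacy, subjective norm and intention are, since they concern the patient's stance towards the people in question. Knowledge is a 30-question test with right and wrong answers, so it is largely unaffected.

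**Step 3: illustrate the size.** The plan has no figure of its own to reproduce here. Its 78 per group rests on transplant proportions that the article does not give, and this point does not depend on it.

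Inputs:
- n = 80 per arm, from the target of 160 patients (160/2, assuming equal allocation).
- Two-sided alpha 0.05 (Sample size calculation).
- Assumed: no true effect; a setting shift of b SDs in those who answer on the spot; and a fraction f of experimental patients who do so. The documents give none of these, nor any scale SD.

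Formulas, for a normal-approximation comparison of two means on one outcome:
- Standard error = SD × √(2/80) = 0.158 SD.
- z = (b × f)/0.158.
- False-positive rate = 1 − Φ(1.96 − z) + Φ(−1.96 − z).

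Worked case, b = 0.2 and f = 1: z = 0.2/0.158 = 1.26. The rate is 1 − Φ(0.70) + Φ(−3.22), which is 24.4% with unrounded values.

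| Assumed shift (SD) | All on the spot (f = 1) | Half on the spot (f = 0.5) |
|---|---|---|
| 0 | 5.0% | 5.0% |
| 0.1 | 9.7% | 6.2% |
| 0.2 | 24.4% | 9.7% |
| 0.3 | 47.5% | 15.8% |
| 0.5 | 88.5% | 35.3% |

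With 78 per arm, shifts of 0.2, 0.3 and 0.5 SD give 23.9%, 46.6% and 87.7% (all) and 9.6%, 15.5% and 34.5% (half). The formula is symmetric, so a downward shift gives the same rates with the sign reversed.

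**Step 4: after the change.** With the same setting in both arms the shift in the contrast is zero, the rate returns to 5%, and the sample size is unchanged.

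**The case against.** The strongest reply is that the scene is inferred. The article does not say that anyone answers in view of others. It says when the form is given and that it may be completed then or mailed. Seating and privacy are details that a condensed article may leave to the full protocol. That stands, and a reader should not conclude that answers are given openly in front of family and educators. What the article does fix is the timing and the permission to complete the form there and then, in one arm only.

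Further objections limit the point:

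- **Educators.** A reader might infer that pressure from the educators is one-sided. It is not: they may also hand the form to controls and help them complete it.
- **Invitees.** The donation item is the most striking example, and it is tempting to call it a biased arm comparison. No control invitees are described, and invitees' baseline is taken in the same session, so there is no arm contrast to bias.
- **Direction.** An upward shift looks natural, but the Background says that a main worry of patients is the living donor's health. A patient among relatives could understate willingness to accept.
- **Magnitude.** The shift is assumed, and the mail route dilutes it. The half-exposure column shows by how much.
- **Analysis.** Completion mode can be recorded and examined. Because patients choose it after randomisation, and completion among the gathered network has no control equivalent, this supports a sensitivity analysis but not a full correction.
- **Voluntariness.** The ethical condition concerns participation, and anyone may mail the form. The documents do not show a breach of it.

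The objection to a mail-only rule also has force. It would remove on-the-spot interpreter help and could cost returns, perhaps most among non-Dutch patients, who are half of the target sample.

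**Conclusion.** The concern holds in a limited form. The collection rule allows a response setting in the experimental arm that controls do not have, and the article describes no private completion. Patients' attitude, self-efficacy, subjective norm and intention may therefore carry a network-presence effect in that arm only. For invitees the matter is candour and voluntariness.

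The documents do not show that such an effect occurs, how large it is or which way it runs. The rates in the table rest on an assumed shift, an assumed share answering on the spot, 80 per arm and a simple comparison of means on one outcome. They show that a modest shift would matter: at 0.2 SD the false-positive rate is about double the nominal 5% if half answer on the spot, and nearly five times it if all do. They should not be read as an estimate for this trial. The change is worth making because it is cheap and cannot be made once the data are collected.

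**What to change.** Amend both Control condition and Experimental condition as follows:

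1. The post-measurement is completed individually, out of sight of family, invitees and educators, and returned in a sealed envelope.
2. Both arms have the same permitted routes, return window and reminders.
3. Interpreter help stays available and is given privately. The educator help now allowed for controls is replaced by private help from someone who is not an educator.
4. Invitees are told that their answers are not shown to the patient.
5. Completion mode is recorded for every questionnaire, and a sensitivity analysis by mode is reported for the four outcomes, with the caveat that mode is self-chosen.

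On-the-spot completion need not be banned if it can be done privately, for example in another room, provided that a comparable route is open to controls.

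Cost: a few sentences in two sections, envelopes, one extra data field, slightly more logistics at the session, and private language help for controls as well. Some returns may be lost or delayed; equal reminders in both arms limit this.
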